## 5.4 Other Study Eligibility Criteria Considerations

In order to assess any potential impact on subject eligibility with regard to safety, the Investigator must refer to the relevant document(s) for detailed information regarding warnings, precautions, contraindications, adverse events, and other significant data pertaining to the study product(s) being used in this study. Such documents may include, but not be limited to, the Investigator's Brochure (IB) or equivalent document provided by Admedus Vaccines Pty Ltd.

Subjects will be required to suspend all HSV-2 medication for one week prior to commencing the Baseline Shedding Assessment at Visit 2 and for duration of the trial. This includes anti-viral medications.

Subjects will not be permitted to have any vaccinations during their participation in the study.

Blood donation must be avoided up to Week 25 (Visit 17).

### 5.4.1 Contraception

All women of child bearing potential (defined as sexually mature women who have had menses within the preceding 24 months and have not undergone hysterectomy, bilateral oophorectomy or tubal ligation) must have a negative pregnancy test (with a sensitivity of at least 50 International Units/mL) performed at Screening and prior to each scheduled vaccination.

Women of child bearing potential must agree not to attempt to become pregnant or undergo in vitro fertilization and, if participating in sexual activity that could lead to pregnancy, must use two reliable methods of contraception simultaneously while receiving protocol-specified medication and for 28 days after stopping the medication. Male subjects must agree to use two reliable methods of contraception simultaneously while receiving protocol-specified medication and for 28 days after stopping the medication if their partner is of child bearing potential.

A combination of two of the following methods must be used:

- Condoms (male or female) with or without a spermicidal agent
- Diaphragm or cervical cap with spermicide
- Intra Uterine Device
- Hormonal-based contraception.

Women who are not of reproductive potential (who have been postmenopausal for at least 24 consecutive months or have undergone hysterectomy, bilateral oophorectomy or tubal ligation) are not required to use contraception.

Male subjects and the partners of female heterosexual subjects will be required to use condoms to protect them from infection in the absence of anti-viral medications.

Since all subjects must cease taking anti-viral therapy for at least 7 days prior to Visit 2 and throughout the study, all subjects will be encouraged to use condoms to prevent infection to their partners if they are sexually active. Anti-viral therapy will only be permitted if the Investigator believes that it is in the subject's best interest to commence this and only after the Sponsor has provided documented approval. Antiviral therapy may not be commenced within 7 days of the shedding assessments and during the shedding assessments. Please refer to Section 6.4.9.

#### **5.4.2 Renal Function**

Renal function eligibility will be determined using an estimated creatinine clearance calculated by Cockcroft-Gault Formula.

The Cockcroft-Gault Formula is:

$$\text{Creatinine clearance (mL/min)} = \frac{(140 - \text{age}) \times (\text{Bodyweight in kg}) \times (0.85 \text{ if female})}{72 \times \text{Serum creatinine (mg/dL)}}$$

#### **5.5 Subject Enrolment**

Before subjects may be entered into the study, Admedus Vaccines Pty Ltd requires a copy of the site's written human research ethics committee (HREC)/Research Governance approval of the protocol, informed consent form, and all other subject information, as applicable. All subjects or legally acceptable representatives must personally sign and date the consent form before enrolment.

All subjects who provide written informed consent will be sequentially assigned a Subject Number. This number will be used to identify the subject throughout the clinical study and must be used on all study documentation related to that subject. Subjects who meet the inclusion/exclusion criteria will be randomly assigned to treatment using a permuted block randomization.

All initial screening tests and procedures (except for the Run-in shedding assessment) should be performed within the 14 days prior to Visit 2, unless otherwise indicated. Randomization and enrolment will be conducted as described in Section 6.3.1 and 6.3.2.

##### **5.5.1 Rescreening**

Subjects with laboratory abnormalities that are exclusionary, but inconsistent with previous history, may be re-tested once. Rescreening of these subjects must be discussed and agreed with the Admedus Vaccines Pty Ltd or designee.

## 6 SCHEDULE OF ASSESSMENTS AND PROCEDURES

### 6.1 Study Schedule of Evaluations

The schedule of assessments is presented in Table 1.

### 6.2 Visit Windows

Every effort should be made to keep to the study schedule. To allow for some flexibility visit windows have been defined and are dependent upon the study stage. The visit windows are as follows:

Table 2– Visit Windows

| Study Period     | Acceptable Window                                          |
|------------------|------------------------------------------------------------|
| Screening/Run-in | ± 3 days                                                   |
| Study Period 1   | ± 3 days except for Visit 5 which has a window of ± 7 days |
| Study Period 2   | ± 3 days                                                   |
| Follow up        | ± 5 days                                                   |

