 Safety assessments to be performed prior to investigational vaccine/placebo.

 Vital signs to be performed prior to investigational vaccine/placebo administration at 30 minutes and 60 minutes following each dose.

 Urine pregnancy testing will be conducted in female participants at Screening, before each administration of study vaccine and at the end of study visit. If positive, a serum pregnancy will be conducted and the vaccine will not be administered.

|               |                                                                                                                                                                                                                                                                      |
|---------------|----------------------------------------------------------------------------------------------------------------------------------------------------------------------------------------------------------------------------------------------------------------------|
|   | To be repeated as deemed necessary by site staff                                                                                                                                                                                                                     |
|   | Subject to document daily whether any HSV-2 symptoms have occurred during the shedding assessments. Following receiving the investigational vaccine/placebo, the subject to document the existence and nature of any injection site reactions that occur for 7 days. |
|   | Visit window is +/- 3 days                                                                                                                                                                                                                                           |
|   | Visit window is +/- 5 days                                                                                                                                                                                                                                           |
|  | Subjects to be either contacted via phone or visit clinic to assess swabbing technique. If subject has had difficulties in collecting swabs since Visit 2, the subject is to be re-educated.                                                                         |

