#### **6.3.2.2 Visit 6 (Week 1) and 8 (Week 5)**

The subject will return to the clinic one week following the investigational vaccine/placebo at Week 1 and 5. The following procedures will be performed:

- Symptom directed physical examination (see Section 6.4.2);
- Review and collection of the Injection Site Reaction Diary (see Section 6.4.11);
- Collection of blood samples for:
  - Haematology (see Section 6.4.5);
  - Clinical chemistry (see Section 6.4.5);
- Blood samples for immunological assessments including:
  - ELISpot (T cell responses specific for HSV-2 gD2) (see Section 6.4.5);
  - Visit 8 only; Exploratory Immune assays (see Section 6.4.5).
- Adverse event, occurrences of HSV-2 outbreaks and concurrent medication questioning (see Section 7 and 8);
- If the subject has evidence of a hypersensitivity type reaction at their injection site(s) photographs will be taken in a standardized manner (see Section 6.4.8)

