##### Injection Site Reaction Diary:

---

The aim of this Diary is to collect information about injection site reactions for 7 days following each vaccination. Information that is to be collected includes the presence of:

- Pain/tenderness;
- Swelling/induration;
- Erythema; or
- Other findings.

Subjects will be provided with a ruler to enable the subject to measure and record the size of any injection site reactions that occur in millimetres (mm). Subjects will be instructed to measure the longest diameter of the reaction area. Instructions on the measurement of reactions will be provided to the subjects within their Diary booklet. Injection site reactions will be graded in accordance with the FDA Guidance for Industry document entitled *Toxicity Grading Scale for Healthy Adult and Adolescent Volunteers Enrolled in Preventive Vaccine Clinical Trial* (2007) except for pain and tenderness (see Section 9.2.1).

The Injection Site Reaction Diaries will be issued and collected at the following visits:

- Vaccination 1- Issued at Visit 5, collected at Visit 6;
- Vaccination 2- Issued at Visit 7 and collected at Visit 8;
- Vaccination 3 – Issued at Visit 9, reviewed at Visit 10, and collected at Visit 11; and
- Booster Vaccination/Placebo – Issued at Visit 16 and collected at Visit 17.

When each Diary is returned by the subject, the site staff will check that it is complete and legible while the subject is in the clinic.

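### A visit inside its window can end the 7-day injection-site diary at day 4, because no rule keeps the diary open until day 7

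*Protocol*

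**What the plan says.** **Length of the record.** Protocol 6.4.10: "The aim of this Diary is to collect information about injection site reactions for 7 days following each vaccination". Sections 6.3.2.1, 6.3.2.3 and 6.3.3.2 repeat the daily 7-day instruction at each dosing visit. The items are pain or tenderness, swelling or induration, erythema and other findings. Subjects measure reactions in millimetres with a ruler.

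**Collection.** Section 6.4.10 lists "Vaccination 1- Issued at Visit 5, collected at Visit 6" and "Vaccination 2- Issued at Visit 7 and collected at Visit 8", then Visit 11 for the third dose and Visit 17 for the booster. Section 6.3.2.2 places Visits 6 and 8 one week after dosing ("The subject will return to the clinic one week following the investigational vaccine/placebo at Week 1 and 5") and lists "Review and collection of the Injection Site Reaction Diary" among their procedures. Sections 6.3.2.5 and 6.3.3.3 do the same for Visits 11 and 17.

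**Windows.** Table 2 in 6.2 allows Study Period 1 visits ± "3 days except for Visit 5 which has a window of ± 7 days". Its Study Period 2 row, which covers Visit 17, also gives ±3 days. The schedule footnote for both periods agrees: "Visit window is +/- 3 days". The only exceptions in these periods are Visit 5 (±7 days) and Visit 10 (±12 hours).

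**Early visits.** Section 6.3.2.4 says the diary goes back to the subject after review at Visit 10. No such instruction is given for Visits 6, 8, 11 or 17. Section 6.4.10 has staff check a returned diary for completeness, but gives no step for days not yet reached.

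**The concern.** Diary length and planned collection time are both exactly 7 days, so there is no slack. Any visit in the early half of its window comes before the diary is due to end, and the text then has the diary collected anyway.

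The diary supports the primary endpoint in 4.2, incidence and severity of local reactions, and it is the only daily, ruler-measured record of them. If it stops at day 4, a reaction that begins, grows or persists on days 5 to 7 has no daily measurement. Subjects would also be observed for different lengths of time, depending on when they attended. With 15 COR-1 and 5 placebo subjects per injection regimen, a few short diaries would be visible in the descriptive tables.

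**Working it through.** This is day arithmetic. No power or error-rate figure is involved.

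**Inputs.** Diary length 7 days (6.4.10). Dosing and collection days from Table 1, with weeks converted to days. Window ±3 days (6.2, Table 2; Table 1 footnote).

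**Step 1: planned gap = collection day − dosing day.** The result matches the stated 7-day diary for every dose.

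**Step 2: permitted gap = 7 ± 3**, with the window counted from the actual dose.

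| Dose | Dosing day | Collection visit (day) | Planned gap | Permitted gap | Next clinic visit (day) |
|---|---|---|---|---|---|
| 1 | 0 | Visit 6 (7) | 7 − 0 = 7 | 4 to 10 | Visit 7 (28) |
| 2 | 28 | Visit 8 (35) | 35 − 28 = 7 | 4 to 10 | Visit 9 (56) |
| 3 | 56 | Visit 11 (63) | 63 − 56 = 7 | 4 to 10 | Visit 12 (84) |
| Booster | 168 | Visit 17 (175) | 175 − 168 = 7 | 4 to 10 | Visit 18 (196) |

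**Step 3: largest loss per dose.** 7 − 4 = 3 days, and 3/7 = 43%.

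**Step 4: sensitivity to how entries are counted.** The protocol does not say whether the injection day is the first entry, or whether an entry is made on the visit day. For a day-4 visit:
- injection day not counted, visit-day entry made: 4 entries;
- injection day not counted, no visit-day entry: 3 entries;
- injection day counted, visit-day entry made: 5 entries;
- injection day counted, no visit-day entry: 4 entries.

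The range is 3 to 5 of 7, with 4 as the central figure.

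**Step 5: time to the next planned clinic inspection.** 28 − 7, 56 − 35, 84 − 63 and 196 − 175 are each 21 days after the planned collection visit. Counted from a visit held 3 days early, the interval is 24 days. No scheduled clinic visit falls on days 5 to 7 to replace the missing entries.

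**Step 6: effect of the change.** If the diary cannot be closed before day 7, all seven entries can be made wherever the visit falls in its window.

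**The case against.** The strongest reply is that the window moves the visit and does not shorten the diary. The 7-day duty is stated at every dose, staff must check completeness, and handing a diary back is already practised at Visit 10. A careful site might well do the right thing. But the protocol gives the hand-back only for Visit 10 and lists collection at the other visits, so a site that takes the diary on day 4 has followed it.

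Several stronger readings are tempting, and the protocol does not support them:

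- *The diary is the main source for the primary endpoint.* Section 8.2 calls the diary booklets supporting documentation. Section 6.4.2 has sites inspected and reactions graded at each visit after Visit 5, and captured as adverse events.
- *Late or persisting reactions are missed altogether.* A reaction present on day 4 is graded at that visit and followed as an adverse event (8.4). One that begins on days 5 to 7 can still be reported at later questioning or on the Observation Form (6.3.1.2). What is lost is daily measured detail.
- *Duration is part of the primary endpoint.* Section 4.2 names incidence and severity only. Onset and resolution dates are recorded for adverse events (8.2.1).
- *Systemic symptoms are cut short too.* Section 8.2 mentions them for diary booklets in general, but the items listed for this diary in 6.4.10 are local plus other findings.
- *The vaccine will look safer than it is.* The same windows apply to COR-1 and placebo, and nothing shows that early attendance differs by arm.
- *The gap could shrink to one day.* If both visits floated ±3 days around Day 0, the arithmetic for doses 2, 3 and booster would give 7 − 3 − 3 = 1 day. Sections 6.3.2.2, 6.3.2.5 and 6.3.3.3 tie the collection visit to the vaccination itself, so 4 days is the better-supported minimum.

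The peak at 48 hours (6.4.11) falls before day 4, which limits the impact. It describes reddened thickening, though, not pain or tenderness. The Phase I size analysis in 3.2.4 used photographs at one and two days only, so it does not show what happens on days 5 to 7.

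**Conclusion.** The point holds in limited form. The 7-day diary, its collection visits and their ±3-day window are not reconciled. A compliant visit can end the daily solicited record at day 4, a worst-case loss of 3 of 7 days (43%) per dose, or 2 to 4 days depending on how entries are counted.

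This assumes that windows run from the actual dose and that the diary is collected at the visit as written. It is a maximum. Section 6.2 asks sites to keep to the schedule, and the protocol gives no basis for estimating how often visits would be early. A reader might infer a loss of 12 of 28 days over the four vaccinations (4 × 3 of 4 × 7), but that needs all four visits at the earliest permitted day.

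At stake are daily measured data for days 5 to 7 and equal observation time, in support of the primary endpoint. Detection of reactions as such, and the comparison between arms, are not shown to be compromised. This is a cheap improvement, not a flaw that undermines the safety analysis.

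**What to change.** Add to 6.4.10: if the collection visit falls before day 7 after vaccination, the diary is reviewed and handed back as at Visit 10, completed through day 7, and returned at the next clinic visit, where staff check for seven daily entries. State also whether the injection day is the first entry.

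The cost is a sentence or two. The downside is that some diaries come back later, up to about 3 weeks after the planned collection visit.

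Two alternatives are weaker. A window of 0 to +3 days for Visits 6, 8, 11 and 17 would also close the gap, but it would restrict the ELISpot and safety blood samples at those visits and the start of swabbing at Visits 11 and 17. The prepaid mail packs in 6.4.9 are among the swab supplies, and swabs go directly to the central laboratory, so they are not a ready route for returning diaries to the site.

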### 6.3 Study Procedures / Assessment Periods

The study procedures to be conducted for each subject enrolled in the study are listed below. Additional information on the study procedures is provided in Section 6.4.

Additional visits and/or assessments may be conducted as clinically indicated. For these additional assessments, data may be collected on unscheduled Case Report Form (CRF) pages provided, together with all adverse events (AEs) and concurrent medication that must be recorded throughout the study period.

There are 4 main study periods:

Table 3– Study periods

| Study Period     | Visit          |
|------------------|----------------|
| Screening/Run-in | Visits 1 to 4  |
| Study Period 1   | Visit 5 to 14  |
| Study Period 2   | Visit 15 to 19 |
| Follow up        | Visit 20 to 22 |

Any deviation from protocol procedures will be noted in the Source Documents and the Sponsor will be notified. The Human Research Ethics Committee/Research Governance for each site will be notified according to their local requirements. Protocol deviations will be reviewed by the study team prior to breaking the blind and deviations will be classified as major or minor.

All laboratory safety tests on blood and urine samples will be performed at local laboratories. Viral shedding assessments and immunological assessments will be performed at a central laboratories specific to the particular assays utilised. . *Refer to the Study Reference Manual.*

Additional visits and/or assessments may be conducted as clinically indicated.

### 6.3.1 Screening/Run in visits

#### 6.3.1.1 Visit 1/Screening

Subjects will be screened within 73 days prior to randomisation to determine eligibility for participation in the study.

The following will be performed and documented at Screening:

- Obtain written informed consent. (This must be completed prior to any other procedure)
- Demographic data (see Section 6.4.1);
- A screening medical/surgical history including HSV-2 history (see Section 6.4.1);
- Review of inclusion/exclusion criteria (see Section 5.2 and 5.3);
- A complete physical examination including:
  - Forearms to be examined and assessed for suitability for ID injections (see Section 7.4.3);
  - Vital signs (see Section 6.4.3);
  - Bodyweight (see Section 6.4.1);
  - Height (see Section 6.4.1);
  - Assessment of all appropriate body systems to determine study eligibility including genital region (see Section 6.4.2);
- Concurrent medication assessment (see Section 7);
- Electrocardiogram (see Section 6.4.4);
- Blood samples for
  - Haematology (see Section 6.4.5);
  - Clinical chemistry including renal function (see Section 6.4.5);
  - Coagulation (see Section 6.4.5);
  - Viral serology for HIV, Hepatitis B and C, HSV-1 and HSV-2 (see Section 6.4.5);
- Urine samples for urinalysis and pregnancy (see Sections 6.4.5 and 6.4.6)

Where possible, it will be requested that the subject will arrange for their local doctor to provide documented evidence of HSV-2 diagnosis and HSV-2 recurrence history.

Subjects meeting the initial inclusion criteria and none of the exclusion criteria will be contacted to arrange Visit 2. Please note, if the subject has been taking anti-viral medications, they will be instructed at this time to cease taking them for the duration of the study. Visit 2 will be scheduled at least 7 days after ceasing the antiviral medications.

#### 6.3.1.2 Visit 2 / Day - 45

At Visit 2, the subject will be provided with education in regard to swab collection, diary completion and outbreak management (See sections 6.4.9, 6.4.10 and 9.10). The site will provide the subject with:

- Swabbing materials including materials for the Run-in shedding assessment and HSV-2 Outbreak kits;
- Written instructions for obtaining genital swabs (gender specific),
- HSV-2 Symptoms and Swabbing Diary and
- Written instructions in case of an HSV-2 Outbreak (*HSV-2 Outbreak Diary*).

Study compliance will be emphasized. The Baseline shedding assessment will commence on the day of Visit 2 in the clinic under supervision of site staff. Subjects will be encouraged to take swabs at the same time each day where possible. (See section 6.4.9).

Adverse event and concomitant medication questioning will be performed. Subjects will be provided with a *Concurrent Medication Form* and *Observation Form* so that they can record information about

medications taken and adverse events between visits. These forms will be reviewed at each clinic visit as part of the adverse event and concurrent medication questioning.

#### **6.3.1.3 Visit 3 / Day - 43**

Visit 3 is scheduled two days after Visit 2. This visit can be performed either onsite or via telephone. The purpose of this visit is to ensure that subject is complying with the daily swabbing procedures. The Investigator or designee will question the subject in relation to their swabbing technique, HSV-2 Symptoms and Swabbing Diary completion and the occurrences of HSV-2 outbreaks. If there is any uncertainty regarding the subject's compliance, the subject will be asked to come in for an onsite visit for re-education.

Adverse event and concurrent medication questioning will also take place at this visit (see Section 7 and 8)

